### Methods: monitoring

#### Data monitoring and harms

Due to the minimal risks of the study and nature of the intervention, there is no formal Data Safety Monitoring Board. On a monthly basis, the two study arms will be compared for event rates, including side effects and their severity, as well as distinguishing medication-related from other side effects.

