### Usual care

Standard of care for LTBI patients at this clinic includes an initial discussion of medication risks, benefits, and side effects. Treatment usually involves daily self-administration of medication for a prolonged period of therapy. Treatment typically involves taking rifampin 600 mg daily for 4 months or isoniazid 300 mg daily for 9 months. If a patient agrees to treatment, they are given a 30-day supply of medication. Subsequent follow-up involves monthly clinic visits, at which time there is an assessment of symptoms, side effects, and adherence; blood-work is performed; and another month’s supply of medication is provided. The usual practice of care with regard to adherence is a phone reminder prior to the next appointment.

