### Outcome measures

All outcomes will be assessed through in-person participant visits or collection from clinic records. Questionnaires will be completed by trained interviewers who are blinded to participant allocation.

The primary feasibility outcomes are summarized in Table 1.

**Table 1 Tab1:** Feasibility outcomes

Outcome	How assessed	Target
Recruitment	How many approached by clinic, how many referred, how many study eligible, how many consented; why ineligible or refused; how long to recruit each patient	40% recruitment rate, based on recruitment of all eligible
Retention	How many drop out at each monthly time point, who and why	70% retention rate
Patient satisfaction and acceptability	Patient perceptions, satisfaction, and acceptance of the intervention through pre- and post-surveys	75% satisfaction rate based on positive responses to questionnaires

While this pilot study will not have the power to detect differences in efficacy, efficacy outcomes will be measured to test procedures for early indication of a promising intervention. The primary efficacy outcome is the difference in proportion of participants completing treatment in each of the study groups. Successful treatment completion is defined as taking at least 80% of the doses of rifampin prescribed within 20 weeks [43]. Estimates of treatment completion will be used to indicate whether the treatment appears promising and to estimate sample size for a future definitive trial. Additional secondary outcomes include proportion of missed visits out of total scheduled visits; the number and length of delays in medication refill; number of missed doses; overall length of treatment (time to dropout); and self-reported adherence. While potentially overestimating true adherence, self-reported adherence is a robust measure of adherence [44, 45]. A brief pre-survey and more detailed semi-structured interviews will be conducted with all individuals to qualitatively assess preferences, attitudes, and satisfaction with the study, as well as barriers to adherence.

The following assessments will be completed by participants (Fig. 1), as per the SPIRIT Statement [46].

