**Fig. 2 Fig2:**
[figure not shown]
Sample visit protocol, 4-month regimen

Participants will be prospectively followed until treatment completion or dropout. We will define participants as lost to follow-up if they are unable to be traced per clinic protocol (two phone calls and a certified letter). The research coordinator will maintain a log documenting refusals and reporting recruitment numbers.

Detailed semi-structured interviews will be conducted with all individuals during their final visit to qualitatively assess preferences, attitudes, and satisfaction with the study intervention. User attitudes will be assessed for both the texting intervention and phone reminder system. Text group participants will be asked for reasons for non-response. These might include forgetting to text back, being too busy, personal reasons, or not understanding the protocol. Treatment defaulters, as assessed through chart review, will be asked for non-adherence reasons and satisfaction with various reminder systems through a one-time phone interview. All interview guides will have been piloted during staff training and presented by an interviewer familiar with the language or else with the aid of an interpreter service. Participants will be asked whether messages are useful and acceptable, whether they found the message text and format to work, and are of preferred quantity, frequency, and timing of use. Information will also be collected to better understand initial expectations and whether attitudes had changed towards the intervention throughout the process. In addition, they will be asked whether they would like to keep using the text message reminders after the study and whether they would recommend the text message reminder system to others. We anticipate including some redundancy of questions to assess internal consistency of responses. We will also collect (a) demographic characteristics of participants, (b) perceived benefits of, and barriers to, LTBI treatment completion, (c) self-efficacy to complete treatment, (d) perceived susceptibility to TB disease, (e) satisfaction with provider interactions and patient education, and (f) preferred reminder system, including whether phone sharing might have affected the intervention and perceptions of costs.

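### Graded side effects in participants who stop attending have no described route into the monthly between-arm harm comparison, so what it records can depend on attendance

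*Protocol article*

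**What the plan says.** - **Data monitoring and harms.** There is no formal safety monitoring board. "On a monthly basis, the two study arms will be compared for event rates, including side effects and their severity"; medication-related and other side effects are to be told apart. No data source or denominator is named.
- **Usual care.** "Subsequent follow-up involves monthly clinic visits, at which time there is an assessment of symptoms, side effects, and adherence". No other point at which side effects are assessed is described.
- **Outcome measures.** "All outcomes will be assessed through in-person participant visits or collection from clinic records". Table 1 records, as a retention outcome, who drops out at each month and why, with a 70% retention target.
- **Data collection, management, and analysis** (text after the Fig. 2 caption). "Participants will be prospectively followed until treatment completion or dropout". Absent participants are traced by two calls and a certified letter before being counted as lost. Treatment defaulters "will be asked for non-adherence reasons and satisfaction with various reminder systems through a one-time phone interview".
- **Statistical methods.** Reasons for dropout are described as part of feasibility.
- **Study objectives.** The definitive trial is to test, among other things, whether texting reduces missed appointments. **Outcome measures** makes missed visits a secondary outcome here.
- **Background** (adherence to therapy). Potential side effects are listed among the reasons for low adherence.

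**The concern.** Set together, these sections make the recording of graded side effects depend on coming to the clinic. The intervention is meant to change how often participants come, and the article itself treats side effects as a cause of stopping. Someone who stops because of a side effect and does not return may leave a reason in the dropout log or in the defaulter call. Neither source is described as recording severity or drug-relatedness, which the harm comparison needs, and neither is described as entering that comparison.

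This is the only harm comparison in the article. If the details are not asked for when the participant is reached, analysis cannot restore them. The pilot is also meant to supply the design of a larger trial, so a gap in how harms are collected could be carried forward untested.

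**Working it through.** The article states no side-effect rate, attendance rate or precision for harms, so there is no figure to reproduce. The check asks how far recording could depart from the truth when the arms do not truly differ.

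**Inputs from the article:** 40 participants allocated 1:1, so about 20 per arm; regimens of 4 or 9 months with monthly visits, so m = 4 or 9; 70% retention target, so up to 0.30 × 40 = 12 participants could leave with the target still met.

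**Assumed inputs:** true monthly side-effect risk s = 5%, 10% or 20%, equal in both arms; attendance a = 60%, 70% or 80% under usual care and 90% with texts.

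**Step 1: risk per participant, recorded only at attended visits.** Recorded risk = 1 − (1 − s·a)^m. Half-width of the risk difference = 1.96·√[p₀(1−p₀)/20 + p₁(1−p₁)/20].

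Example with s = 10%, m = 4, attendance 80% and 90%:
- Usual care: 1 − (1 − 0.08)⁴ = 0.284
- Text: 1 − (1 − 0.09)⁴ = 0.314
- Risk ratio 1.11; risk difference 3.1 points (from unrounded risks); half-width 28.4 points
- True risk in both arms: 1 − 0.90⁴ = 0.344

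Over all values of s and m:

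| Attendance, usual care vs text | Spurious risk ratio | Spurious difference (points) | 95% half-width (points) |
|---|---|---|---|
| 80% vs 90% | 1.05–1.12 | 1.8–4.6 | 22.7–30.9 |
| 70% vs 90% | 1.12–1.27 | 3.5–9.5 | 22.1–30.9 |
| 60% vs 90% | 1.22–1.47 | 5.4–14.9 | 21.5–30.7 |

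The largest spurious difference (14.9) is below the smallest half-width (21.5).

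**Step 2: rate per attended visit.** Expected recorded events are s·a·m over a·m visits, which is s whatever the attendance. Missed visits alone then cause no bias.

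**Step 3: non-return caused by the side effect.** If a share q of those with a side effect do not come back, the recorded risk among attenders is s(1−q)/(1−s·q). With s = 10%:
- q = 30% in both arms: 0.07/0.97 = 0.072 in each. The ratio is 1.00, but both arms fall short of the true 0.10.
- q = 50% usual care, 25% text: 0.05/0.95 = 0.053 and 0.075/0.975 = 0.077. The ratio is 1.46 (1.42–1.48 over s = 5–20%).
- The same shares the other way round: 0.053/0.077 = 0.68.

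A per-visit denominator therefore does not recover the lost events. The comparison between arms can go either way, depending on quantities the article does not give.

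**The case against.** The best defence is that the article does not lose sight of people who stop. It logs why they drop out, traces them, phones defaulters about their reasons, and collects perceived barriers to completion. A side effect is an obvious answer to such questions. Clinic records are also a named source and could hold unscheduled contacts. Figs. 1 and 2 and the interview guides are not available here and may list more. Both arms receive the same clinic-prescribed drugs with monthly review, the intervention is a reminder text, harms are not a listed outcome, and this is a feasibility pilot.

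Much of this stands. It rules out three stronger readings that a reader might infer:

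- **That side effects are recorded only at attended visits, or that defaulters' answers are kept out of the comparison.** The article is silent on both points.
- **That the comparison is biased.** The denominator is unstated, and Steps 2 and 3 show that bias depends on it and on differential non-return. Better adherence could also raise true drug exposure, so an excess with texts would not be purely an artefact.
- **That the direction reverses and nearly half of events are missed.** Such an example can be built. Take 20 per arm, 4 visits for completers and 2 for dropouts, completion of 50% and 70%, and 10% reporting per visit. That gives 20 × (0.5×4 + 0.5×2) = 60 visits with 6.0 events, and 20 × (0.7×4 + 0.3×2) = 68 visits with 6.8 events. Assuming that half of the 10 and 6 dropouts had an event nobody learned of gives totals of 11.0 and 9.8, with 5/11 = 45% missed under usual care. But both arms show 0.10 per attended visit, so a reversal needs raw counts or per-participant rates, and the 45% is put in by assumption.

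The defence does not show where severity and drug-relatedness would be recorded for someone who stops attending, or that such events reach the comparison.

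**Conclusion.** The point holds as a gap in described ascertainment. The monthly comparison can under-record side effects in participants who stop attending, and can do so unequally between arms because attendance is what the intervention aims to change. Neither direction nor size can be derived from the article. Under the assumed rates above, with risk counted per participant, the spurious difference is about 2 to 15 points and is swamped by chance error of about 22 to 31 points at 20 per arm. The reason to act is therefore not a likely false signal in this pilot. Details not asked for at the one planned later contact cannot be recovered, and the same procedure may be taken into the definitive trial. This is a cheap improvement, not a flaw that threatens the pilot's feasibility aims.

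**What to change.** 1. In **Data collection, management, and analysis**, add the clinic's side-effect questions, with severity and drug-relatedness, to the one-time call to treatment defaulters, in both arms.
2. In **Data monitoring and harms**, state that events learned from that call, and dropouts whose recorded reason is a side effect, are included in the monthly comparison, flagged by source (visit or phone).
3. Report the comparison with observed time or attended visits, and with the number of participants not reached, by arm. The choice between the two denominators is a lesser reporting matter; either should be named.

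The cost is a few questions on a call already planned and a sentence or two of text. The downside is that recall by phone is less precise than assessment at a visit, which is why the source should be flagged. Participants who cannot be reached remain unobserved, so their number has to be shown.

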#### Auditing

All research staff have received human subjects research training and will receive appropriate training in recruitment, data collection, and management. Ongoing study progress will be tracked with regular monitoring by the PI with study and clinic personnel, training of all staffs involved in the process, monthly research team meetings, and regular review to ensure that study targets are being met.

#### Confidentiality

The web management application (PRiM) is password-protected, and data can be stored in encrypted format when texting other subjects. Texts are addressed to de-identify usernames, and pass through the website, thus keeping identities private—other subject’s phone numbers are never seen by subjects—as all contacts are indirect through the web application. Only HIPAA-trained researchers are allowed to access or download the data via the website.

## Discussion

Treatment adherence and completion rates for latent tuberculosis infection remain suboptimal across high-risk groups. This study is the first, to our knowledge, to assess the feasibility and acceptability of text messaging as an adjunct to usual care for treatment for LTBI in the USA. Strengths of this study include an adequate recruitment period, provision of an incentive that will help balance concerns related to messaging costs, and in-depth and ongoing collection of process measures.

Some limitations and challenges of this study are the messaging cost for participants, the risk of participants running out of plan minutes, and the possibility that participants change numbers or service providers. Voice calling and text messaging are equally affected by changing phone numbers, and text messaging might be advantageous if a patient is running low on plan minutes. We will recommend that the clinic ask participants about their phone plan at each visit. Participants may miss appointments no matter the intervention, and we recognize the possible limitations of self-reported adherence, including the fact that reporting during the week prior to an appointment may not reflect adherence patterns over time, since participants may become more adherent right before an appointment [53]. Finally, there is possible selection bias of enrollees, since participants must have a phone and be willing to text. Participants may also need to be comfortable with the communication style in order to effectively show behavior change [27]. We will compare our demographic and clinical data to those of non-enrollees, in order to ensure generalizability of our findings.

As a result of this pilot study, we will advance knowledge regarding best practices regarding adherence for treatment of latent TB infection. As this is a pilot study, we recommend results be interpreted with caution. Further intervention studies should verify the results of this study and scale up the proposed approach to broader populations and clinical sites.

## Abbreviations

LTBI: Latent tuberculosis infection
PCHD: Pima County Health Department
PRiM: Platform for Research Integrated Messaging
REDCap: Research electronic data capture
TB: Tuberculosis
